# 2.3. Rationale for study population

The enrolled patients should satisfy the following inclusion criteria, and not meet any exclusion criterion. In addition to following criteria, the patient should also be excluded if there is any contraindicated medical condition or use of incompatibility drug during basic treatment period.

# 2.3.1 . Inclusion criteria

1. Provision of signed informed consent prior to any study specific procedures;
2. Male or female, aged ≥18 years at the time of consent;
3. Established documented diagnosis of heart failure for at least three months ago according to “Chinese Heart Failure Diagnosis and Treatment Guideline” issued by the Chinese Medical Association Cardiovascular Branch.
4. Left ventricular ejection fraction (LVEF) ≤40% (echocardiogram, radionuclide, ventriculogram, contrast angiography or cardiac MRI );
5. NYHA cardiac functional grading II to III, with stable clinical symptoms; including those diagnosed as grade IV within 2 weeks before enrollment;
6. Serum NT-proBNP ≥ 450pg/ml;
7. Those who have received standardized baseline treatment regimens without doses adjusted and given intravenously for at least two weeks prior to enrollment;
8. standardized drug treatment includes: angiotensin-converting enzyme inhibitor (ACEI) or angiotensin receptor blocker (ARB) or angiotensin receptor neprilysin inhibitor (ARNI), beta blocker, and aldosterone receptor antagonist (the optimal therapeutic dose should be achieved, except for contraindications or intolerance);

# 2.3.2 . Exclusion criteria

1. Patients should not enter the study if any of the following exclusion criteria are fulfilled
2. Heart failure caused by valvular disease, congenital heart disease, pericardial disease, arrhythmia or non-cardiaogenic disease, or caused by vital organ failure (such as renal, hepatic failure, etc.); and right heart failure caused by pulmonary or other definite causes; and acute heart failure;
3. Coronary revascularization (percutaneous coronary intervention [PCI] or coronary artery bypass grafting [CABG]) or cardiac synchronization therapy planned to undergo after randomization, or had received cardiac resynchronization therapy prior to enrolment;
4. Any condition outside the CV diseases such as but not limited to malignant tumor, severe mental illness, hematopoietic diseases, neuroendocrine system disease, liver transaminase and alkaline phosphatase ≥ 3 x upper limit of normal (ULN), abnormal renal function serum creatinine > 2 mg/dl (176.82 umol/L), potassium >5.5mmol/L;
5. Patient with left ventricular outflow tract obstruction, myocarditis, aortic aneurysm, aortic dissection, or obvious hemodynamic changes caused by unrepaired valve;
6. Cardiogenic shock, uncontrollable malignant arrhythmia, sinus or atrioventricular block at second degree type II or above without pacemaker treatment, progressive unstable angina pectoris or acute myocardial infarction;
7. uncontrolled hypertension systolic blood pressure (SBP) ≥ 180mmHg and/or diastolic blood pressure (DBP) ≥ 110mmHg; or SBP < 90mmHg and/or DBP <60mmHg;
8. Participation in another clinical study with an IP during the last month prior to enrolment;
9. Women of child-bearing potential (i.e., those who are not chemically or surgically sterilized or who are not post-menopausal) who are not willing to use a medically accepted method of contraception that is considered reliable in the judgment of the investigator, from the time of signing the informed consent throughout the study and 4 weeks thereafter, OR women who have a positive pregnancy test at enrolment or randomisation OR women who are breast-feeding;
10. Allergic constitution; known to be allergic to research drug;
11. Inability of the patient, in the opinion of the investigator, to understand and/or comply with study medications, procedures or any conditions may render the patient unable to complete the study.

# 2.4. Patient enrolment and Follow-up visit

Patients who fail to meet the eligibility criteria should not, under any circumstances, be enrolled or receive study medication. Patient should receive at least 2 weeks of standardized treatment. Patient should not receive other traditional Chinese medicine or Chinese patent medicine (with similar function and composition with Qiliqiangxin Capsules).

Patients meet the inclusion criteria can enter the randomization. During this period, the drug and dosage are fixed for each patient. If it is necessary to make adjustment, it should be recorded in the case report form (CRF).

Patients should visit the hospital for efficacy and safety assessment during the 1st, 3rd, 6th, 9th, and 12th months after the random grouping until the study finish.

# 2.5. Discontinuation of investigational product (IP)

At any time after randomization, patients are free to discontinue for any reason. Discontinuation from IP is not the same as complete withdrawal from the study. Study drug treatment can be discontinued when:

1. The patient can stop treatment at any time;

2. The patient has allergic reactions that are clearly associated with the IP;

3. The patient has occurrence of symptoms, signs and/or abnormal examination results that are related to the IP, or the condition determined by the investigator to terminate the study;

4. Pregnancy during the study;

During the trial, the patient should take the standard dose of the IP as long as possible. The patients should resume taking the IP as soon as possible after the relevant causes are excluded and follow up as planned. Generally AEs, SAEs and potential endpoint events should not lead to IP discontinuation, unless there is a clear clinical rationale to do so.

Conversely, patients stopped taking the IP should also participate and complete in the study follow up and evaluation items. Patients that intent to discontinue will always be asked about the reason(s) and the presence of any AEs. If the patient is unable to participate in the study visit, follow-up should be continued by phone as planned to determine if any adverse events and endpoints have occurred unless the patient refuses to follow up and withdraw from the study.

# 2.6 Withdrawal

The patient has the right to withdraw from the study at any time for any reason. The researcher should retrieve the remaining IP when the patient withdraws. The reason for the withdrawal should be acquired by follow-up interview or telephone. Follow-up should be continued in order to ascertain whether any endpoints or safety events have occurred. Optimally, patients who discontinue from IP should continue to attend all study visits according to plan until study finish as much as possible. Information should be recorded in the Case Report Form.

# 2.7. Discontinuation of the study

1. The overall study may be stopped due to the following reasons:

- Base on Data Safety Monitoring Committee (DSMC) interim analysis results;
- Researchers find serious safety problems;
- Major mistakes in the study protocol;
- The sponsors decide to suspend study due to management problems or lack of funding;
- The competent administrative department cancels the experiment, and half-stops all studies.

1. The discontinuation of the study can be temporary or permanent. During the suspension, all study records should be kept for inspection.

# 3. Treatment

# 3.1 Investigational products (IP)

**Study drug:** Qiliqiangxin Capsule (芪苈强心胶囊)

-Ingredients: Astragalus, ginseng, monkshood, Danshen, Pepperweed Seed, rhizoma alismatis, radix polygonati officinalis, cassia twig, red flower, cortex periplocae, tangerine peel

-Property: Capsule; the contents are brown to black brown granules; bitter in taste;

-Specification: 0.3g/ granule

-Bach number: GYZZ Z20040141

-Manufacturer: Shijiazhuang Yiling Pharmaceutical Co., Ltd

**Placebo:** Qiliqiangxin Matching Placebo

-With identical color, specification, packaging, , property of contents and other features with Qiliqiangxin Capsule

# 3.1.1 Package and label

The appearance of small package is shown below and will be labeled with “For QUEST study only”. Each package contains 36 capsules sealed in aluminum-plastic plates.

[figure not shown]

Big package: White paper box, with size of 29.5cm╳12cm╳22cm, each big package includes 33 small packages.

Each is marked with following label:

| **Qiliqiangxin in Heart FailUre: AssESsment of Reduction in MorTality (QUEST)**  **(For Clinical Study Only)** |
| --- |
| **Package No.: XXXXX**  [Lot number] xxxx [Expiry date] xxxx |
| [GYZZ] Z20040141  [Pakcage] 33 small boxes, and 36 granules in each small box (amount for 99-days)  [Directions] Three times a day and four granules each time  [Storage] Sealed in a cool dry place. Please store the product out of children's reach. |
| **Please be sure to follow doctor's orders and visit at the specified date to the hospital for follow-up evaluation. Thank you for your cooperation!** |

# 3.1.2 . Storage

All IP should be kept in a secure place under appropriate storage conditions. Each center must assign a committed staff to preserve and manage the study drug.

# 3.1.3 Accountability

The IP provided for this study will be used only as directed in the study protocol. Patients will be asked to bring all unused study medication and empty packages to the study. During each follow-up, the investigator or delegate will collect and check the amount of returned capsule and fill in Drug Distribution Form, timely and accurately to account for all IP dispensed to and returned from the patient, in order to determine the compliance of subjects at each site visit.

At the end of study, all remaining drugs should be returned. Undistributed IPs should be sealed when returned. Remaining drugs should be retained and uniformly destroyed after study.

During each follow-up, the subjects should return all remaining drugs, and researchers must make an inventory of remaining drugs and keep record

# 3.2. Study plan and timing of procedures

# 3.2.1 . Enrolment period (day -14 to day 0):

The investigators review the inclusion and exclusion criteria. Patients who do not meet these criteria must not be randomized into the study. During enrolment period the following assessments and procedures will be completed.

-Demography (date of birth, sex, race, ethnic group) and relevant medical and surgical history, including smoking history, will be recorded.

-General physical examination (vital signs, NYHA classification, appearance, cardiovascular systems [including edema], etc.)

-Laboratory samples will be collected and sent to the central laboratory

-ECG and echocardiogram will be recorded

# 3.2.2 Randomization and Treatment period (day 0 to 12 months [with maximum of 36 months]):

The dispensing date of the IPs is regarded as day 0. Patients will be randomized into the study or control group in a 1:1 ratio w

ith the basis of current standardized treatments for chronic heart failure. The study drug is recommended to be taken about 30 minutes after meals, three times a day as follow.

-Study group: Standardized treatment of chronic heart failure + Qiliqiangxin Capsules (4 capsules/time, 3 times/day);

-Control group: Standardized treatment of chronic heart failure + Placebo Capsules (4 capsules/time, 3 times/day);

This study does not allow dose adjustments. If the patient miss to take the IP in a day, the accumulated dose for the next day should not exceed the daily dose. If the patient has an intolerable adverse event, which is relevant to study drug according to the judgment of researcher, the patient should terminate the following treatment with the study drug.

Do not take drugs at home on the morning of visit day. Investigators will review laboratory results received from the past visit(s). If the patient has experienced any potential endpoints, SAEs, DAEs and/or AEs of interest since the last visit, these should be recorded in the CRF.

# 3.3 Concomitant medications and other treatments

All patients should be treated according to regional standard of care for HF and other comorbidity(s). Also, cardiac and heart failure related procedures will be captured during the study. Background medication will not be provided by the Sponsor.

1. Detailed recording of medications related to HF, HTN as well as other relevant cardiovascular medications (e.g., statins, antihypertensive and antithrombotic agents) will be made throughout the study;
2. Traditional Chinese medicines have similar contents to the test drug should not be used during the entire treatment period after entering the randomization period;
3. Patients should receive dietary guidance for heart health, such as low-salt diet, moderate drinking, etc. Patients should also receive counseling for appropriate lifestyle improvements such as weight monitoring, physical exercise, smoking cessation, and alcohol withdrawal.
4. No drug has been found to be prohibited with use of Qiliqiangxin Capsules.

**3.3.1 Heart failure medications**

According to local HF treatment guidelines, or the “Chinese Heart Failure Diagnosis and Treatment Guide 2018” issued by the Chinese Medical Association Cardiovascular Branch, the specifications are as follows:

1. Patients should remain on stable doses of medications which will allow assessment of incremental QLQX effect. No intravenous injection of diuretic, cardiac stimulant or vasodilator substance at least two weeks before enrollment;
2. Patient should receive standardized drug treatment of chronic heart failure at least two weeks before randomization grouping stage, and all drugs should be adjusted to fixed dosage. Standardized drug treatment includes: angiotensin-converting enzyme inhibitor (ACEI) or angiotensin receptor blocker (ARB) or angiotensin receptor neprilysin inhibitor (ARNI), beta blocker, and aldosterone receptor antagonist (the optimal therapeutic dose should be achieved unless contraindicated or not tolerated);

3) After entering the treatment period, Dose reduction or discontinuation of proven effective therapies should be avoided unless all other measures fail to improve the patient’s situation.. If there is any need for adjustment, reason and regimen change should be recorded in the CRF.

# 3.4 Adverse drug reaction

Adverse reactions to test drugs are not known. The National Adverse Reaction Monitoring Database showed the possible reactions might included gastric discomfort such as nausea, bloating, and hiccups, etc.

# 3.5 Evaluation on compliance

In order to determine the compliance of subjects, the administration (drug distribution and recovery) of all investigational products should be recorded in the appropriate sections of the eCRF.. The actual dosage should be within 80%-120% of predefined dosage.

# 4. Outcome Measures for Analyses

# 4.1 Clinical observation endpoints

# 4.1.1 . Primary outcome measure

- - - The composite endpoint events consisting of cardiovascular death
    - Re-hospitalization due to the worsening of heart failure;

# 4.1.2 . Secondary outcome measures

- All-cause mortality
- Secondary endpoint events (given up treatment due to worsening heart failure, successful resuscitation after cardiac arrest, malignant arrhythmia, non-fatal stroke)
- Cardiovascular death and re-hospitalization due to worsening heart failure in patients with ischemic heart disease
- Level of Serum NT-proBNP

*Note: All endpoint events should be determined and reviewed by Clinical Event Adjudication Committee.*

# 4.2. Safety outcome measure:

- Adverse events (Serious Adverse Events [SAEs], Discontinuation of IP due to Adverse Events, etc.)
- AEs of interest (volume depletion, renal events, etc.)
- Clinical laboratory indexes: blood routine test (hemoglobin, red blood cells, white blood cells, platelets), routine urine test (urinary protein, urinary white blood cells, urine red blood cells), serum biochemistry (urea nitrogen, creatinine, blood uric acid, total protein, albumin, alanine aminotransferase, aspartate aminotransferase, alkaline phosphatase, total bilirubin, fasting blood glucose, potassium, sodium, chlorine, total cholesterol, triglycerides, low density lipoprotein, high density lipoprotein).
- 12-lead ECG
- Physical examination

# 5. Course of Study

All participants, including those discontinue study drug prior to completion of study, should continuously take all planned visits listed in the table until the end of study. If a visit is postponed or taken in advance, it should not affect the next visit. The next visit should be carried out in accordance with the original planned time.

[figure not shown]
×¹ Simplified physical examination

- ×* Cardiac ultrasound and 12-lead ECG within the first 6 months of enrollment;
- UNS (unplanned visit): (x) The marked item is optimal and performed according to the judgment of researchers.
- EOS (final visit): Make arrangement according to the study end time (if there is a visit within one month before the end of study, it is regarded as a final visit, but needs to be supplemented with the items required completely)
- Pregnancy test is only applicable to women of childbearing age (if the urine pregnancy test is positive, it must be confirmed by serum pregnancy test).

# 6. Efficacy Assessments

# 6.1. Endpoint reporting overview

When potential endpoint events have been identified, the researchers should collect all relevant support documents within 7 days and report to CEA committee. Investigators will record the incident in endpoint report form and submit supporting data in a timely manner (admission and discharge records, medical records, death records, ECG, etc.). The potential endpoints event (All deaths, All HF events [hospitalizations for HF or urgent HF visits], cardiac ischemic events [MI and unstable angina], cerebrovascular events [stroke and TIA], etc.) will be reviewed for central CEA process.

CEA committee consists of a chairman and 5-6 members. Each case will be independently reviewed by two members of the committee. The conclusions will be submitted to the chairman of the committee.

# 6.2 Potential endpoint events

For each potential endpoint event, the investigator or delegate will record information in the CRF

- **Hospitalization for heart failure:**

1. The patient was hospitalized for HF diagnosed preliminarily;

2. The patients who were in hospital extended at least 24 hours (or if the hospitalization time and discharge time were not available, it should indicate change of calendar date);

3. Record on the patient report that there are new symptoms or worsening symptoms due to HF, including at least one of the following:

a. Difficulty breathing (difficulty breathing on exertion, difficulty breathing on resting, orthopnea, paroxysmal breath with difficulty at night)

b. Reduced exercise tolerance

c. Fatigue

4. The patient had objective evidence of an acute exacerbation of HF, including at least two health examination results or a health examination result and at least one laboratory standard, including:

a. Determine the health examination results caused by HF, including new or deteriorated:

1) Peripheral edema; 2) Abdominal distension or increase of ascetic fluid (in the absence of primary liver disease); 3) Lung rales and/or crackles; 4) Increased jugular venous pressure and/or hepatojugular reflex (+); 5) S3 galloping; 6) Clinically significant or rapid weight gain, having relation with fluid retention;

b. Laboratory evidence of new or worsening HF obtained within 24 hours, including:

1) Increased concentration of B-type natriuretic peptide (BNP) / N-terminal B-type natriuretic peptide precursor (NT-proBNP) consistent with acute decompensated HF (eg.: BNP > 500 pg/ml or NT-proBNP > 2000 pg/ml); In patients with long-term elevation of natriuretic peptides, special attention should be paid to a significant increase beyond baseline. 2) Imaging evidence of pulmonary congestion; 3) Non-invasive diagnostic evidence of clinically significant increase in left or right ventricular filling pressure or decreased cardiac output; echocardiographic criteria includes: E/e ́>15 or D leading pulmonary venous inflow pattern, congestive inferior vena cava with minimal inspiratory collapse, or reduction of small stroke distance (time velocity integral; TVI) at left ventricular outflow (LVOT). 4) Invasive diagnostic evidence: right heart catheterization showed pulmonary capillary wedge pressure (pulmonary occlusion pressure) ≧ 18mmHg, central venous pressure ≧ 12mmHg, or cardiac output index;

*Note: If applicable, all results in the diagnostic check need to be reported; even if the above criteria are not met, results might provide important information for the determination of the above events.*

5. The patients receive an initial or intensive treatment for HF, including at least one of the following:

a. Enhance the treatment of oral diuretics;

b. Intravenous diuretics or vasoactive drugs (such as positive inotropic drugs, vasopressors or vasodilators);

c. Mechanical or surgical intervention, including:

1) Mechanical circulation support (e.g.: Intra-aortic balloon pump, ventricular assist device, extracorporeal membrane oxygenation, total artificial heart);

2) Mechanically assisted removal of body fluids (e.g.: ultrafiltration, hemofiltration, and dialysis);

- **All-cause mortality:** For the purpose of the efficacy analysis, death will be subclassified and recorded as CV or Non-CV death in the CRF
- **Cardiovascular death:** including death caused by acute myocardial infarction (AMI), sudden cardiac death, acute decompensated heart failure, stroke, cardiovascular (CV) surgery, CV bleeding, and other CV inducing death;
- **Given up treatment due to the worsening of HF:** Worsening of heart failure symptoms and signs, requiring intravenous drug or mechanical support treatment, and patients or family members voluntarily give up treatment or left hospital without cure; if the result of follow-up is death, it is included in heart failure death.
- **Successful resuscitation after cardiac arrest**
- **Malignant arrhythmia：**There is no uniform standard for the definition of malignant arrhythmia. It generally refers to arrhythmia that can cause severe hemodynamic disorder in a short period of time, causing syncope or even sudden death. According to this standard, malignant arrhythmia mainly has the following categories: (1) severe bradyarrhythmia, such as severe sick sinus syndrome, high or third degree atrioventricular block; (2) tachyarrhythmia, such as persistent ventricular tachycardia, ventricular flutter, ventricular fibrillation, atrial flutter/atrial fibrillation with rapid ventricular rates, atrioventricular reentry tachycardia, pre-excitation syndrome with atrial fibrillation, sinus tachycardia, etc.
- **Non-fatal stroke**

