# 9.2.3 . Efficacy analysis:

- PP analysis and FAS analysis were performed simultaneously with efficacy evaluation;
- Main efficacy evaluation index is the time when a composite endpoint event (cardiovascular death and re-hospitalization for deterioration of heart failure) occurs. The lack of primary endpoint events is considered as censored data.

The main research hypotheses are:

H0: λT / λC ≥ 1

H1: λT / λC < 1

λT and λC are the risk of endpoint events in the study group and control group respectively. The Kaplan-Meier method was used to estimate the incidence of clinical endpoints, and a Log rank test was performed for analysis between the two groups. COX proportional hazard model was used and the center was served as a covariate to estimate the hazard ratio and the 95% confidence interval. The composite endpoints, cardiovascular death and rehospitalization for deterioration of heart failure, were analyzed separately.

- - Secondary efficacy indicators:
    - All-cause mortality
    - Composite endpoints (given up treatment due to worsening heart failure, successful cardiac arrest after resuscitation, malignant arrhythmia, non-fatal stroke)
    - Cardiovascular death and re-hospitalization for decompensated heart failure in patients with coronary heart disease
    - Serum NT-proBNP: statistical analysis of measurement data between groups.

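### The malignant arrhythmia definition in Section 6.2 lists sinus tachycardia and an open-ended set of tachyarrhythmias with no per-event test, so benign or persisting rhythms can enter the secondary composite

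*Protocol*

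**What the plan says.** Section 6.2 of the protocol begins its entry on malignant arrhythmia with a concession: "There is no uniform standard for the definition of malignant arrhythmia". It then gives a general standard: "It generally refers to arrhythmia that can cause severe hemodynamic disorder in a short period of time, causing syncope or even sudden death". The step from standard to list reads "According to this standard, malignant arrhythmia mainly has the following categories", and two categories follow.

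- Slow rhythms: "severe bradyarrhythmia, such as severe sick sinus syndrome, high or third degree atrioventricular block".
- Fast rhythms: ventricular tachycardia (if persistent), ventricular flutter and ventricular fibrillation, and then "atrial flutter/atrial fibrillation with rapid ventricular rates, atrioventricular reentry tachycardia, pre-excitation syndrome with atrial fibrillation, sinus tachycardia, etc".

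Malignant arrhythmia is one of four components of a secondary endpoint. Section 4.1.2 lists them as "given up treatment due to worsening heart failure, successful resuscitation after cardiac arrest, malignant arrhythmia, non-fatal stroke", and Section 9.2.3 analyses the same four as a composite. A note in Section 4.1.2 sends every endpoint event to the adjudication committee.

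At entry, Section 2.3.2 (item 6) excludes malignant arrhythmia that cannot be controlled, and "sinus or atrioventricular block at second degree type II or above without pacemaker treatment". Item 2 excludes heart failure that is caused by arrhythmia.

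**The concern.** The standard and the list do not agree. The standard describes rhythms that bring sudden, severe circulatory failure. The list includes sinus tachycardia with no qualifier, although in a heart failure patient this may reflect no more than fever. Because the standard speaks of what a rhythm can cause, it does not oblige anyone to show that the rhythm did harm in the patient concerned. The list is also left open at the end.

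What is at stake is how the secondary composite can be read. If low-grade rhythms unrelated to treatment are counted beside resuscitated arrest and stroke, a null result may hide an effect on the serious components, and a positive one cannot be attributed to them. Without a fixed rule, two adjudicators could classify the same tracing differently and both be following the protocol.

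**Working it through.** The protocol gives no event rate, effect size or power for malignant arrhythmia or for the secondary composite, so there is no figure to reproduce. The check is mainly a comparison of passages.

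**1. Per-event criteria within Section 6.2**

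| Requirement | Hospitalization for heart failure | Malignant arrhythmia |
|---|---|---|
| New or worsening | Yes, symptoms due to heart failure | Not stated |
| Minimum duration | Yes, 24 hours in hospital | Not stated, apart from the word persistent for ventricular tachycardia |
| Objective threshold | Yes, examination and laboratory evidence | No rate or other threshold |
| Consequence or treatment | Yes, started or intensified treatment | Potential consequence only |

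The same section thus sets a full per-event test for one endpoint and none for the other.

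**2. List against standard.** Sick sinus syndrome must be severe, block must be high or third degree, ventricular tachycardia must be persistent, and atrial flutter or fibrillation must be rapid, though no rate is given. Sinus tachycardia carries no qualifier at all.

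**3. List against entry criteria.** Section 2.3.2 removes heart failure caused by arrhythmia, uncontrollable malignant arrhythmia, and unpaced block of second degree type II or above. It does not remove atrial fibrillation as a comorbidity, sinus tachycardia, or paced high-grade block. A listed rhythm can therefore be present at entry and persist into follow-up.

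**4. Adjudication.** Section 6.1 has two committee members review each case independently. Its examples of events for central review are deaths, heart failure, ischaemic and cerebrovascular events; arrhythmia is not named. The protocol gives the committee no arrhythmia criteria beyond those in Section 6.2.

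**5. Direction of the effect (illustration only).** Assumptions: hazard ratio (HR) 0.80 on genuine events; added events occur equally in both arms; f is the share of control-arm composite events unaffected by treatment; 200 genuine events in all; two-sided 0.05; 1:1 allocation.

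- Composite HR ≈ 0.80(1 − f) + f
- Genuine control-arm events: 200/1.8 = 111.1
- Added events per arm: n = 111.1 × f/(1 − f); total events D = 200 + 2n
- Power = Φ(|ln HR| × √D/2 − 1.96)
- Events needed for 80% power = 4(1.960 + 0.842)²/(ln HR)²

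| f | Composite HR | Total events | Power | Events for 80% power |
|---|---|---|---|---|
| 0 | 0.80 | 200 | 35% | 631 |
| 10% | 0.82 | 225 | 32% | 798 |
| 25% | 0.85 | 274 | 27% | 1,189 |
| 50% | 0.90 | 422 | 19% | 2,829 |

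With 400 genuine events, power falls from 61% to 56%, 48% and 33%. These rows show only that adding events with no treatment effect pulls the hazard ratio towards 1. Nothing in the protocol says which row, if any, applies.

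**The case against.** The best defence is that the general standard governs and the list only illustrates it, so that a listed rhythm counts only when it meets the standard. Every event is also adjudicated from source records and ECGs, and Section 7.2.1 foresees events being judged negative. This has force: a reader might infer that any listed rhythm counts automatically, and the text does not establish that. Such rhythms can count. What remains is that the standard speaks of potential rather than actual consequence, and the committee is given nothing else to apply.

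Three further inferences go beyond the documents.

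- **That a patient with a chronic rhythm already meets the endpoint on day 0.** Section 3.2.2 records potential endpoints experienced since the last visit, which points to on-study occurrences. It does not say how a persisting rhythm is to be handled, so the gap is real but narrower.
- **That block in general counts.** The text limits it to high or third degree, and unpaced block of second degree type II or above is excluded at entry. Only paced patients could bring it in with them.
- **That benign rhythms would dominate the composite, with a known loss of power.** No component rate is given, and the figures above rest wholly on assumptions. The trial was sized for the primary endpoint only, so modest power for this composite is not in itself a fault.

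**Conclusion.** The point holds in a limited form. Section 6.2 names rhythms that do not fit its own standard, leaves the list open, and sets no per-event test of onset, worsening or consequence. Benign or persisting rhythms can therefore enter the secondary composite, and adjudicators have no fixed rule. That conclusion rests on the text alone.

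Dilution is the likely direction if the added rhythms are unaffected by treatment, which is an assumption. Its size cannot be derived from the protocol. The primary endpoint and its planned 620 events do not depend on this definition. The correction should be made, but it does not threaten the trial's main conclusion.

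**What to change.** In Section 6.2, and in the adjudication committee's charter, before unblinding:

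- Delete sinus tachycardia and the open ending of the list.
- Count an event only if it is newly documented, or worsened relative to baseline, after randomisation **and** is either (i) persistent ventricular tachycardia, ventricular flutter or fibrillation, high or third degree atrioventricular block, or severe sick sinus syndrome; or (ii) another listed tachyarrhythmia with documented severe haemodynamic disorder or syncope, as the protocol's own standard describes.
- State that a rhythm or paced block already present at baseline is not an event unless it worsens to meet that standard.
- Record arrhythmias that are not counted as adverse events, and as serious adverse events when they meet those criteria. Section 7.2.1 generally exempts malignant arrhythmia from serious adverse event reporting, so narrowing the definition also narrows that exemption.

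This changes how events are classified, not how patients are treated. The cost is a wording amendment, fewer counted events in the secondary composite, and some additional serious adverse event reporting.
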